## Abstract

Parkinson’s disease (PD) neuropathology is marked by the selective loss of dopaminergic neurons in the substantia nigra pars compacta, accompanied by the widespread involvement of central and peripheral structures. Brain-derived neurotrophic factor (BDNF), a neurotrophin crucial for the survival of dopaminergic neurons, plays a pivotal role in neuronal and glial development, neuroprotection, and the modulation of synaptic plasticity. Repetitive transcranial magnetic stimulation (rTMS), a non-invasive technique, enhances neurotransmitter release, trans-synaptic efficacy, signaling pathways, gene transcription, neuroplasticity, and neurotrophism. Evidence supports that high-frequency rTMS increases BDNF expression and improves task-specific cognitive deficits in PD patients. This article outlines a detailed protocol to investigate whether rTMS targeting the dorsolateral prefrontal cortex bilaterally induces changes in plasma BDNF levels, the plasma-derived exosomal BDNF concentration, and executive functions in individuals with PD. Identifying non-invasive interventions that effectively modulate the neurobiological mechanisms underlying cognitive and behavioral functions is critical for addressing cognitive impairments and mitigating disease progression in the PD population. This study aims to advance translational research by identifying biomarkers and developing therapeutic strategies for future applications in neurodegenerative diseases.

## 1. Introduction

Parkinson’s disease (PD) is one of the most common neurodegenerative diseases, second only to Alzheimer’s disease (AD) [1], characterized by motor and non-motor symptoms including cognitive deficits such as executive dysfunction, which worsen with disease progression and contribute significantly to patient burden.

These deficits are linked to the degeneration of dopaminergic (DAergic) neurons in the nigrostriatal pathway, which is more pronounced in PD patients with mild cognitive impairment (PD-MCI) than in those without cognitive abnormalities. However, PD-MCI patients had the relative preservation of other dopaminergic systems in the brain compared to PD patients with dementia [2], making PD-MCI patients more suitable for focused rehabilitative approaches.

Neurotrophins are endogenous proteins responsible for the development, function, and survival of neurons [3]. The expression of neurotrophins in the brain is downregulated in postmortem PD patients [4,5], and the supplementation of neurotrophin has demonstrated neuroprotective effects in animal studies on PD and clinical trials [6].

Among these neurotrophins, brain-derived neurotrophic factor (BDNF) has garnered significant attention due to its role in dopaminergic neuron survival, synaptogenesis, and plasticity [7]. It supports the survival and function of DAergic neurons by increasing the number of tyrosine hydroxylase (TH)-positive neurons and enhancing dopamine secretion [8] in the striatum and substantia nigra [9,10]. 

Notably, reduced BDNF expression in the substantia nigra and striatum in PD patients has been implicated in disease progression, with the presence of low blood BDNF levels emerging as a potential biomarker for disease severity [4,5].

BDNF plays a key role in cognition, with reduced activity-dependent expression impairing executive functions (EFs) linked to hippocampal-prefrontal circuitry [11]. Impairment in this circuitry due to reduced BDNF expression can exacerbate cognitive deficits in PD. Studies, such as Angelucci et al. (2015), have demonstrated that cognitive rehabilitation can improve EFs and increase serum BDNF levels in PD-MCI patients, supporting the hypothesis that targeting BDNF could enhance cognitive outcomes in this population [12].

Emerging research has highlighted extracellular vesicles (EVs)—which mediate cell-to-cell communication and can cross the blood–brain barrier—as potential carriers of BDNF. These EVs, particularly exosomes, are critical for biomarker validation as they provide insight into central nervous system processes [13]. PD patients exhibit elevated plasma EV concentration and altered EV surface antigens, which correlate with disease severity and cognitive impairment [14].

Plasma exosomes, the smallest EVs, carry BDNF, making them ideal candidates for investigating neurotrophic changes associated with interventions like repetitive transcranial magnetic stimulation (rTMS) [15]. 

Specifically, low plasma exosomal BDNF levels have been associated with greater motor severity and functional impairments in PD patients, as reported by Chung et al. (2020). These findings underscore the importance of studying how rTMS-induced changes in BDNF levels, particularly those mediated by exosomes, might relate to clinical outcomes in PD [15]. Nevertheless, the role of EVs on the BDNF expression in PD warrants further investigation.

Repetitive transcranial magnetic stimulation (rTMS) is a non-invasive intervention that has been shown to regulate the expression of neurotrophic factors, including BDNF, by promoting neuronal differentiation, survival, and plasticity [16]. 

For instance, Choung et al. 2021 demonstrated that high-frequency (HF) rTMS enhanced BDNF expression in a model of Alzheimer’s disease alongside improvements in neural survival markers [15]. The neuroprotective and neuroplastic benefit of rTMS has been observed in studies across various neurological diseases including major depression [17], amyotrophic lateral sclerosis [18], and PD [19,20].

HF-rTMS targeting the dorsolateral prefrontal cortex (DLPFC)—a region crucial for EFs—has consistently shown promise in modulating BDNF expression and improving cognitive functions. EF abnormalities in PD are closely linked to frontal lobe damage, particularly in the DLPFC, which undergoes the progressive degradation of DAergic neurons [21].

Taken together, this evidence suggests that TMS has the potential to modulate plasma BDNF levels and exosomal BDNF concentrations, offering a non-invasive strategy to address both motor and cognitive symptoms in PD.

Our proposed protocol aims at investigate whether HF-rTMS treatment for 4 weeks, targeting the right and left DLPFC, can increase plasma BDNF and plasmatic EV-derived BDNF concentration and improve EFs in PD patients. 

## 2. Primary and Secondary Outcomes

### 2.1. Primary Outcomes

#### 2.1.1. Change in Plasma BDNF Levels

We will evaluate the changes in plasma BDNF levels after 4 weeks of rTMS treatment in patients with PD-MCI compared to PD-MCI patients receiving sham rTMS treatment and those receiving no rTMS treatment.

#### 2.1.2. Change in Plasmatic EV-Derived BDNF Concentration

We will assess the changes in plasmatic EV-derived BDNF concentrations after 4 weeks of rTMS treatment in PD-MCI patients relative to PD-MCI patients receiving sham rTMS treatment and those receiving no rTMS treatment.

#### 2.1.3. Change in EF Performance

We will measure the changes in executive function performance after 4 weeks of rTMS treatment in PD-MCI patients compared to PD-MCI patients receiving sham rTMS treatment and those receiving no rTMS treatment.

### 2.2. Secondary Outcomes

#### 2.2.1. Sustained Changes in Plasma BDNF Levels

We will assess the changes in plasma BDNF levels 8 weeks post rTMS treatment in PD-MCI patients compared to PD-MCI patients who have received sham rTMS treatment and those who have received no rTMS treatment.

#### 2.2.2. Sustained Changes in Plasmatic EV-Derived BDNF Concentration

We will evaluate the changes in plasmatic EV-derived BDNF concentrations 8 weeks post rTMS treatment in PD-MCI patients relative to PD-MCI patients receiving sham rTMS treatment and those receiving no rTMS treatment.

#### 2.2.3. Sustained Changes in EF Performance

We will determine the changes in EF performance 8 weeks post rTMS treatment in PD-MCI patients compared to PD-MCI patients receiving sham rTMS treatment and those receiving no rTMS treatment.

#### 2.2.4. Correlation Between BDNF Biomarkers and EF Performance

We will investigate the correlation between plasma BDNF levels or plasmatic EV-derived BDNF concentrations and EF scores after 4 weeks of rTMS treatment and 8 weeks post treatment in PD-MCI patients as compared to PD-MCI patients receiving sham rTMS treatment and those receiving no rTMS treatment.

## 3. Materials

### 3.1. Laboratory Measurements, Neurocognitive Assessment, and TMS Intervention

#### 3.1.1. Blood Sampling

All the blood samples will be drawn in the morning after overnight fasting at three time points: before the start of rTMS intervention (baseline), within 1 week after the end of treatment (T1), and within 1 week after the maintenance period (T2).

Blood will be drawn by trained staff from the antecubital vein (gauge of needle: 21 G × ¾″ × 7″, BD Vacutainer, REF 367282; BD, NJ, USA) into 15 vacutainers to ensure sufficient sample collection. Possible confounders for BDNF levels such as sex, age, and BMI will be accounted by statistical analysis and by analyzing multiple measurements at different time points intra subjects.

#### 3.1.2. Plasma BDNF Quantification

1.Centrifugation
Blood samples will be centrifuged at 4 °C for 15 min at 1500× *g* to isolate normal plasma;To obtain platelet-poor plasma, five plasma samples will undergo a second centrifugation step at 10,000× *g* for 10 min at 4 °C [22].
2.Storage
After centrifugation, plasma samples will be aliquoted into Eppendorf tubes (Eppendorf SE, Hamburg, Germany) in single-use volumes and stored at −80 °C until analysis.
3.Analysis
Plasma samples will be analyzed using the mature BDNF Rapid ELISA kit (Cat. # BEK-221, Biosensis, Thebarton, Australia) following the manufacturer’s instructions (Figure 1a);A dilution factor of 1:20 will be used, based on previous findings by Gejl et al. (2019), for optimal detection [22] (Figure 1a).

#### 3.1.3. Plasma-Derived EV Isolation

Plasma-derived extracellular vesicles (EVs) will be isolated following the state-of-the-art procedures according to MISEV 2023 guidelines [23], with key steps detailed below [24] (Figure 1b):
1.Sample preparation
Ten milliliters of platelet-poor plasma will be diluted (1:1000) with PBS to reduce viscosity and facilitate isolation.
2.Sequential Centrifugation
Centrifugation will be performed at 10,000× *g* for 10 min at 4 °C;The supernatant will be transferred to a new container and centrifuged at 20,000× *g* for 10 min at 4 °C to remove cells, dead cells, and debris;EVs will be pelleted by ultracentrifugation at 100,000–110,000× *g* for 70 min at 4 °C. The pellet will be washed with PBS to remove contaminants and resuspended in a small volume of PBS.
3.Sucrose Cushion
For additional purification, exosomes will be floated on a 30% sucrose cushion to eliminate nonspecific protein aggregates and other contaminants.
4.Immunomagnetic Beads
Alternatively, magnetic beads coated with antibodies targeting exosome-specific surface markers (e.g., CD9, CD63, CD81) will be used to isolate EVs directly without ultracentrifugation.
5.Storage
EV-enriched plasma will be aliquoted into single-use tubes and stored at −80 °C until further analysis.

#### 3.1.4. EV Characterization

1.Detection of EV-Specific Markers
The MACSPlex Human Exosome Kit (Miltenyi, Bergisch Gladbach, Germany) will be used. This kit employs 4.8 μm polystyrene beads conjugated with capture antibodies for EV markers;Platelet-poor plasma (60 µL) will be diluted 1:2 in buffer solution and incubated with beads overnight.
2.Analysis
EVs bound to beads will be detected using APC-conjugated antibodies and analyzed on a MACSQuant Analyzer-10 flow cytometer (Miltenyi, Bergisch Gladbach, Germany);A blank control (MACSPlex Buffer + beads + detection antibodies) will measure background signal;Median fluorescence intensity (MFI) for BDNF will be normalized against EV markers (CD9, CD63, CD81) to calculate the normalized MFI (nMFI).
3.Reliability Testing
To ensure specificity, EV enrichment using ultracentrifugation will be compared with samples processed without enrichment.

#### 3.1.5. Quality Control

1.Additional Characterization
Nanoparticle Tracking Analysis (NTA) or Dynamic Light Scattering (DLS) will measure nanoparticle size and concentration;Western blotting for EV markers (TSG101, Alix, Synthenin) will complement the MACSPlex analysis.
2.Statistical Validation
nMFI values will be statistically analyzed across experimental groups, ensuring reproducibility and reliability.

### 3.2. Neurocognitive Assessment

To exclude an operator-dependent effect, the same neuropsychologist will conduct the assessment within subjects and will be blind to group membership to maintain the validity and integrity of the assessment.

Cognitive profile will be investigated with the Behavioural Assessment of the Dysexecutive Syndrome (BADS). It is a comprehensive tool for assessing executive functioning through tasks that simulate real-life scenarios. BADS is particularly effective in identifying executive dysfunctions in patients with brain injuries or neurological conditions such as PD [25].

The impact of PD on patient’s daily life will measured with the self-reported Parkinson’s Disease Questionnaire (PDQ-39) [26].

### 3.3. TMS Intervention

In this project, a two-site rTMS stimulation delivered by a Magstim unit (Magstim Co., Whitland, UK) featuring a double 70 mm cooled coil will be applied.

R-Gr will receive 4 weeks of excitatory rTMS stimulation of the left and right DLPFC; S-Gr will receive 4 weeks of rTMS sham treatment of the left and right DLPFC; and C-Gr will be free of rTMS treatment. For R-Gr and S-Gr, each week of rTMS treatment will consist of five sessions (30 min each [15 min for each region], one per day).

For each target area, the stimulation protocol will comprise 1500 pulses at 15 Hz, formatted as a 3 s train, followed by a 28 s inter-interval at 100% motor threshold (MT) that will be delivered. 

A 15 Hz stimulation frequency will be used, based on its established efficacy in enhancing neuroplasticity and modulating BDNF levels [27,28] including in PD [29].

The stimulation protocol consists of 1500 pulses per hemisphere, applied in a 3-s train, followed by a 28-s inter-train interval. This structure balances efficacy while minimizing participant fatigue and the risk of adverse effects.

The intensity will be set at 100% of each participant’s resting MT to ensure consistent stimulation effects while accounting for individual variability [30]. Adjustments will be made if participants report discomfort. 

Individualized coil positioning will be guided using T1-weighted magnetic resonance imaging MRI volume (sequence parameters: TR = 1900 ms; TE = 2.1 ms; TI = 900 ms; FOV = 240 mm^2^; matrix = 256 × 256; voxel size = 0.9 × 0.9 × 0.9 mm^3^) to accurately localize the DLPFC bilaterally. 

For each site target, the coil will be placed with the junction of the two coil wings above the target point.

Sham stimulation will use the same parameters as real sessions, with a sham coil that mimicks operational noise without delivering actual stimulation.

In both real and sham treatment, the coil position over right and left DLPFC will be constantly monitored using the Softaxic neuronavigation system (Electro Medical Systems, Bologna, Italy) coupled with a Polaris Vicra infrared camera. Each session will last for about 45 min including time for set up and 30 min of stimulation.

### 3.4. Safety Consideration

The rTMS protocol adheres to International Federation of Clinical Neurophysiology safety guidelines.

Adverse Event Monitoring: Participants will be monitored for side effects, such as headaches or scalp discomfort, using standardized reporting tools. Any adverse events will be recorded and managed according to predefined criteria.

Stopping Criteria: If participants experience significant discomfort or side effects that compromise their well-being, predefined stopping criteria will be implemented to ensure safety.

## 4. Experimental Procedures

### 4.1. Project Design

This will be a prospective, double-blind, randomized, controlled single-center study. PD patients that satisfy inclusion and exclusion criteria will be randomly assigned to one of three groups: (1) real group (R-Gr), in which the patients will receive 4 weeks of real rTMS stimulation; (2) sham group (S-Gr), in which the patients will receive 4 weeks of sham treatment of rTMS stimulation; and (3) control group (C-Gr), in which the patients will be free of treatment. Here, participants will receive no rTMS treatment, and this group will serve as a baseline comparator. This group is designed to control for placebo effects and participants’ expectations, which are known to influence outcomes inducing striatal DA release in PD patients [31,32,33].

Each week of rTMS treatment will consist of five sessions (45 min each, one per day).

Blood collection and neurocognitive investigation will be performed at baseline (T0), after 4 weeks from baseline and 4 weeks of rTMS treatment (T1), and 8 weeks after the end of treatment (maintenance period [T2]).

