## 5. Statistical Analyses

### 5.1. Primary Analyses

The baseline demographic, clinical, laboratory measures and cognitive scores will be compared between groups using an ANOVA for continuous variables and Chi-square tests for categorical variables. Covariates such as age and gender will be included if group differences exist at baseline.

A mixed-factorial ANOVA will be conducted to evaluate the effect of the rTMS protocol after 4 weeks of daily stimulation on plasma BDNF levels, the plasmatic EV-derived BDNF concentration, and EF performance. The model will include Group as a between-subjects factor and Time as a within-subjects factor.

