### 6.1. Innovative Design with Dual Control Groups

The inclusion of both sham and placebo control groups in the study design strengthens the ability to discern the specific effects of rTMS from placebo-induced dopamine release, a phenomenon often observed in PD patients due to heightened expectations of treatment efficacy [21,36]. Moreover, by employing a sham coil that replicates the noise and tactile sensations of real rTMS, the study minimizes the risk of participant unblinding, enhancing the internal validity of the findings [21]. Furthermore, the use of neuronavigation, guided by patient-specific MRI sequences, ensures the precise targeting of the DLPFC. This region is integral to EFs and dopaminergic activity, and its precise stimulation reduces variability and enhances the reproducibility of results [19,21]. 

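### The untreated arm is given the sham arm's role as placebo control, and nothing makes real versus sham the deciding contrast, so a shared placebo response could be claimed as an rTMS effect

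*Protocol article*

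**What the plan says.** **Role of the third arm.** Section 4.1 describes C-Gr thus: "participants will receive no rTMS treatment, and this group will serve as a baseline comparator". It then adds: "This group is designed to control for placebo effects", and extends this to patients' expectations, noting that these can trigger striatal dopamine release in Parkinson's disease. Section 6.1 refers to "The inclusion of both sham and placebo control groups in the study design". The trial has only real, sham and untreated arms, so the placebo group there must be C-Gr.

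**Blinding.** Section 4.1 states without qualification: "This will be a prospective, double-blind, randomized, controlled single-center study". Section 3.2 blinds the neuropsychologist to group. The sham coil appears in 3.3, "with a sham coil that mimicks operational noise without delivering actual stimulation", and in 6.1, "employing a sham coil that replicates the noise and tactile sensations of real rTMS".

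**Analysis.** Section 2.1.1 sets real rTMS against both comparators, "compared to PD-MCI patients receiving sham rTMS treatment and those receiving no rTMS treatment", and 2.1.2 and 2.1.3 are built the same way. For the primary mixed-factorial ANOVA, 5.1 says: "The model will include Group as a between-subjects factor and Time as a within-subjects factor". Section 4.4 sizes the trial on a three-group test. Section 5.2 applies a Bonferroni correction for pairwise comparisons to all mixed-factorial models.

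**The concern.** Controlling for placebo and expectation in the real arm requires a comparator that undergoes the same procedure and holds the same expectation. That comparator is sham. An untreated arm shows practice, time and natural-course effects. Sham minus untreated shows how large the placebo response is. Real minus untreated contains both the specific and the placebo effect, and the patients in that comparison cannot be blind.

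The description therefore gives C-Gr a role it cannot fill, and the analysis does not correct this. A three-level Group by Time test is positive when any arm differs, including when real and sham move together away from no treatment. With two comparators of equal standing and no deciding contrast, such a result could be reported as an effect of stimulation. The article's own reasoning makes this relevant: 4.1 links placebo to dopamine release, and 6.3 links dopamine release to BDNF expression and executive function, which are the primary outcomes.

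**Working it through.** **Inputs from section 4.4.** f = 0.25, α = 0.05, power 0.80, correlation r = 0.1, 3 groups, 3 measurements, total N = 66 (about 22 per arm).

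**Assumptions.** The size of a shared placebo response, d, is in SDs of the outcome at one time point; the article gives no value. A second correlation, r = 0.5, shows sensitivity. The divisor of three for Bonferroni is also assumed, since 5.2 gives no number of comparisons.

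**1. The plan's own figure.** For the between-groups factor averaged over m = 3 measurements, λ = f²·N·m / (1 + (m−1)r) with df (2, N−3). At N = 66, λ = 0.0625 × 66 × 3 / 1.2 = 10.31 and power is 0.808. The smallest N is 65 (power 0.802), or 66 with equal arms. The stated 66 reproduces as an omnibus sample size.

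**2. What the omnibus can distinguish.** Noncentrality depends on the sum of squared deviations of the arm means (real, sham, untreated):
- only real differs, (d, 0, 0): (2d/3)² + 2(d/3)² = 2d²/3
- pure placebo, (d, d, 0): 2(d/3)² + (2d/3)² = 2d²/3

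The two are identical. At the effect used for sizing, the omnibus has power 0.808 for either pattern.

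**3. Omnibus on T0–T1 change under pure placebo.** The variance of change is 2(1−r) in SD² units, so λ = 22·(2d²/3) / (2(1−r)), df (2, 63). Example: d = 0.5, r = 0.1 gives λ = 22 × 0.1667 / 1.8 = 2.04.

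| d (SD) | P(omnibus p < 0.05), r = 0.1 | r = 0.5 |
|---|---|---|
| 0.2 | 0.074 | 0.095 |
| 0.3 | 0.106 | 0.156 |
| 0.5 | 0.220 | 0.369 |
| 0.8 | 0.501 | 0.768 |

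In simulation (40,000 runs, r = 0.5) the last two rows give 0.37 and 0.77. Real versus sham tested at 0.05 stays at 0.05 for every d.

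**4. Pairwise tests under the same pattern, three-way Bonferroni (0.05/3 = 0.0167).** Real versus sham is positive in about 1.6–1.8% of simulated trials. Real versus untreated is positive in 12% (r = 0.1) to 22% (r = 0.5) at d = 0.5, and in 32% to 58% at d = 0.8.

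**5. Power of real versus sham if a specific effect exists.** Noncentral t with noncentrality [δ/√(2(1−r))]·√(22/2), where δ is the real-versus-sham difference, at 22 per arm. For δ of about 0.8 SD (0.795, pooled error, 63 df):

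| Level | r = 0.1 | r = 0.5 |
|---|---|---|
| 0.0167 | 0.318 | 0.572 |
| 0.05 | 0.490 | 0.738 |

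Taking exactly 0.8 SD, or a two-arm error term (42 df), moves these by at most about one percentage point. At δ = 0.5 SD and level 0.05, power is 0.23 (r = 0.1) to 0.37 (r = 0.5).

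**The case against.** **A valid test is already planned.** The Bonferroni comparisons in 5.2 cover all mixed-factorial models, so real versus sham will be tested with its error rate kept. This stands. A reader might infer from 5.1 and 4.4 that a significant three-group F is the declared rule for success. No section says so: 5.1 gives a model, and 4.4 gives the basis for sizing. If 2.1 were read as requiring real to beat both comparators, the false-positive risk under pure placebo would be small. But the article does not say that either, and step 4 shows that real versus untreated can be positive on placebo alone.

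**The size depends on an assumed response.** This also stands. Section 4.4 expects only a minimal sham effect, and two of the three primary outcomes are laboratory assays, for which the article supports no particular placebo shift. At 0.2–0.3 SD the omnibus is positive in 7–16% of trials. The larger figures show what could happen and are not a forecast.

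**Blinding is partly protected.** The blinded neuropsychologist limits rating bias in every arm, and the loose label does not bias real versus sham. It does not blind untreated patients to their own allocation.

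**The sham-coil descriptions.** A reader might call 3.3 and 6.1 contradictory. Section 3.3 mentions noise but does not say noise only, so the texts differ in detail without excluding each other. They still need reconciling, because 6.1 rests its claim of reduced unblinding partly on tactile sensation.

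**The untreated arm has value.** It does, for practice and time effects and for sizing the placebo response. Nothing here argues for dropping it.

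**Conclusion.** The concern holds in this limited form and should be fixed. Two statements are wrong as written: that C-Gr controls for placebo and expectation (4.1, repeated in the label in 6.1), and that the three-arm trial as a whole is double-blind. In addition, no text makes real versus sham decisive, although it is the only contrast that isolates a specific rTMS effect.

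Under a pure placebo response with 22 per arm, the omnibus is positive in 7–9.5% of trials at 0.2 SD, 11–16% at 0.3, 22–37% at 0.5 and 50–77% at 0.8. The ranges run from r = 0.1 to r = 0.5, and the response sizes are assumptions. The equal noncentrality of the two patterns needs no such assumption beyond equal arms. The documents do not support the stronger conclusion that the trial lacks a valid sham comparison.

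**What to change.** **Section 5.1.** State that each primary outcome is decided by the real-versus-sham contrast of change from T0 to T1, tested at that outcome's full level. Test real versus no treatment second, in fixed sequence at the same level. Estimate sham versus no treatment with a confidence interval only. Against an assumed three-way Bonferroni, this raises real-versus-sham power at about 0.8 SD from 32% to 49% (r = 0.1) or from 57% to 74% (r = 0.5).

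**Sections 4.1 and 6.1.** Describe C-Gr as an open no-treatment arm that measures practice and time effects and, set against sham, the placebo response. Restrict the double-blind claim to real versus sham. Make the sham-coil descriptions in 3.3 and 6.1 agree with the coil in use.

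**Cost.** No new patients or procedures are needed to make the change, but it is more than rewording. Real versus no treatment could be claimed only after real versus sham succeeds. The 80% power in 4.4 belongs to the omnibus effect and must be restated: with 22 per arm, real versus sham at level 0.05 has 23–37% power at 0.5 SD and 49–74% at about 0.8 SD. Section 6.3 reports that recruitment has begun, so the change should be made as a dated amendment before any outcome comparison by arm, including the interim analysis in 5.3.
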